**Specific hospital admissions that were preceded by high-risk prescribing**		
AO-1	Patient time with GI risk factors as defined in PO- measures 1 to 6 (Table 4) #	Number of denominator patients admitted with GI bleeding who had any high risk prescription as defined in PO-measures 1 to 6 (Table 4) in the eight weeks before admission
AO-2	Patient time with heart failure as defined in PO-measure 7 (Table 4) #	Number of denominator patients admitted to hospital for HF - exacerbation who had a high-risk prescription as defined in PO-measure 7 (Table 4) in the eight weeks before admission
AO-3	Patient time with renal risk factors as defined in PO-measures 8 to 9 (Table 4)^#^	Number of denominator patients admitted to hospital for acute renal failure or with dehydration or diarrhoea (both defined as potentially inappropriate/ambulatory care sensitive admissions) who had any high-risk prescription as defined in PO-measures 8 to 9 (Table 4) in the eight weeks before admission
**Specific hospital admissions irrespective of high-risk prescribing**		
AO-4	Patient time with GI risk factors as defined in PO-measures 1 to 6 (Table 4)^#^	Number of denominator patients, who are admitted to hospital for GI bleeding
AO-5	Patient time with heart failure as defined in PO-measure 7 (Table 4)^#^	Number of denominator patients, who are admitted to hospital for HF - exacerbation
AO-6	Patient time with renal risk factors as defined in PO-measures 8 to 9 (Table 4)^#^	Number of denominator patients, who are admitted to hospital for acute renal failure or with dehydration or diarrhoea (both defined as potentially inappropriate/ambulatory care sensitive admissions)
**Any cause hospital admissions**		
AO-7	Patient time with GI risk factors as defined in PO-measures 1 to 6 (Table 4)^#^	Number of denominator patients admitted to hospital with any emergency admission
AO-8	Patient time with heart failure as defined in PO-measure 7 (Table 4)^#^	Number of denominator patients admitted to hospital with any emergency admission
AO-9	Patient time with renal risk factors as defined in PO-measures 8 to 9 (Table 4)^#^	Number of denominator patients admitted to hospital with any emergency admission

^# ^The denominator is the time that each patient is defined as having risk factors by virtue of age, disease or co-prescribing in the year before the intervention and the year of follow-up. AO measures 1 to 3 consider specific hospital admissions where patient has had a recent high-risk prescription; AO measures 4 to 6 consider specific hospital admissions irrespective of whether or not the patient has a had a recent high-risk prescription; AO measures 7 to 9 consider all emergency admissions

**Table 7 T7:** Measures of wider impact on NSAID prescribing (VO = Volume outcomes)

VO-1	Total NSAID prescription volume/registered patients in participating compared to non-participating practices
VO-2	Proportion of patients prescribed an NSAID stratified by age in participating compared to non-participating practices

**Key: **NSAID = Non-steroidal anti-inflammatory drug

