### Outcome measures

The outcome measures used are shown in detail in Tables 3, 4, 5, 6, 7 and the levels of analyses (practice versus patient level) are outlined under 'statistical methods'.

**Table 3 T3:** Primary outcome measure (CPO = Composite prescribing outcome)

Number Risk factor (Denominator)		High-risk prescription definition (Numerator)
CPO	Number of patients with any risk factor listed in PO-measures 1 to 9 (Table 4)	Number of patients with any high-risk prescription listed in PO-measures 1 to 9 (Table 4)

**Table 4 T4:** Secondary outcome measures (PO = Prescribing outcomes)

Number Risk factor (Denominator)		High-risk prescription definition (Numerator)
PO-1	Number of patients with a Read Code for peptic ulceration ever recorded	Number of denominator patients prescribed a traditional oral NSAID^¶ ^or low dose aspirin in the previous eight weeks who have NOT been prescribed a gastro-protective drug in the 12 weeks before, or since the most recent NSAID or aspirin prescription
PO-2	Number of patients aged 75 and over	Number of denominator patients prescribed a traditional oral NSAID^¶ ^in the previous eight weeks who have NOT been prescribed a gastro-protective drug in the 12 weeks before, or since the most recent NSAID prescription
PO-3	Number of patients aged 65 and over prescribed aspirin in the previous 12 weeks	Number of denominator patients prescribed a traditional oral NSAID^¶ ^in the previous eight weeks who have NOT been prescribed a gastro-protective drug in the 12 weeks before, or since the most recent NSAID or aspirin prescription
PO-4	Number of patients aged 65 and over prescribed aspirin in the previous 12 weeks	Number of denominator patients prescribed clopidogrel in the previous eight weeks who have NOT been prescribed a gastro-protective drug in the 12 weeks before, or since the most recent aspirin or clopidgrel prescription
PO-5	Number of patients prescribed warfarin in the previous 12 weeks	Number of denominator patients prescribed a traditional oral NSAID¶ in the previous eight weeks who have NOT been prescribed a gastro-protective drug in the 12 weeks before, or since the NSAID prescription
PO-6	Number of patients prescribed warfarin in the previous 12 weeks	Number of denominator patients prescribed low dose aspirin or clopidogrel in the previous eight weeks who have NOT been prescribed a gastro-protective drug in the 12 weeks before, or since the aspirin or clopidogrel prescription

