PO-7	Number of patients with a QOF heart failure code ever recorded	Number of denominator patients prescribed any oral NSAID in the previous eight weeks
PO-8	Number of patients prescribed both a diuretic and an ACE inhibitor/ARB in the previous 12 weeks	Number of denominator patients prescribed any oral NSAID in the previous eight weeks
PO-9	Number of patients with a QOF CKD (stage 3, 4, or 5) code recorded as the most recent CKD code	Number of denominator patients prescribed any oral NSAID in the previous eight weeks
PO-10	**GI risk composite** Number of patients with any risk factors as defined in PO-measures 1 to 6	Number of denominator patients with any high-risk prescription as defined in PO-measures 1 to 6
PO-11	**Renal risk composite** Number of patients with any risk factors in PO-measures 8 to 9	Number of denominator patients with any high-risk prescription as defined in PO-measures 8 to 9

^¶ ^'Traditional' NSAID means all representatives of this class *except *Cox-2 selective agents, such as celecoxib;

**Key: **NSAID = Non-steroidal anti-inflammatory drug; QOF = Quality and outcomes framework; CKD = chronic kidney disease; ACE = angiotensin converting enzyme; ARB = Angiotensin Receptor Blocker

**Table 5 T5:** Secondary outcome measures (Repeated versus new prescribing)

Number	Risk factor (Denominator)	High-risk prescription definition (Numerator)
CPO- Repeated	Number of patients with any risk factor listed in PO-measures 1 to 9 (Table 4)	Number of patients with any high-risk prescription listed in PO- measures 1 to 9 (Table 4) where the patient has received a high-risk prescription in the previous 12 months
CPO-New	Number of patients with any risk factor listed in PO-measures 1 to 9 (Table 4)	Number of patients with any high-risk prescription listed in PO-measures 1 to 9 (Table 4) where the patient has NOT received a high-risk prescription in the previous 12 months

**Table 6 T6:** Secondary outcome measures (AO = Admissions outcomes)

Number	Denominator	Numerator
		Trigger event plus high-risk prescription

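### GI and renal admission outcomes stop following patients who qualify only through a current prescription 12 weeks after it ends, and the intervention can affect when it ends

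*Protocol article*

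**What the plan says.** Table 6 (Outcome measures) lists nine admission outcomes in three risk groups: GI (AO-1, AO-4, AO-7), heart failure (AO-2, AO-5, AO-8) and renal (AO-3, AO-6, AO-9). The footnote defines the denominator as patient time at risk in the year before the intervention and the year of follow-up: "The denominator is the time that each patient is defined as having risk factors by virtue of age, disease or co-prescribing". Numerators are restricted to patients in that denominator. This includes the broadest outcomes, AO-7 to AO-9: "Number of denominator patients admitted to hospital with any emergency admission".

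The risk factors come from Table 4. Some depend on current prescribing:
- PO-3 and PO-4: "Number of patients aged 65 and over prescribed aspirin in the previous 12 weeks"
- PO-5 and PO-6: "Number of patients prescribed warfarin in the previous 12 weeks"
- PO-8: "Number of patients prescribed both a diuretic and an ACE inhibitor/ARB in the previous 12 weeks"

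Others do not end when a drug is stopped:
- PO-1: "Number of patients with a Read Code for peptic ulceration ever recorded"
- PO-2: "Number of patients aged 75 and over"
- PO-7: "Number of patients with a QOF heart failure code ever recorded"
- PO-9: a most recent CKD code of stage 3, 4 or 5

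The informatics tool flags affected patients for review (Intervention component one). Any change in prescribing is left to the practice (Recruitment of patient participants). Under Statistical methods, Patient level analysis, the protocol expects patients to enter and leave denominators over time.

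**The concern.** A flagged combination has a denominator drug and a numerator drug, and a review may end with either being stopped. If the denominator drug goes and nothing else qualifies the patient, follow-up for the GI or renal admission outcomes ends 12 weeks after its last prescription. Whether a patient is still observed then depends on a decision made after the practice started the intervention, and one that the intervention is meant to prompt.

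This matters most for AO-7 and AO-9. No admission outcome is specific to thrombotic events, although antiplatelets appear in PO-1, PO-3, PO-4 and PO-6 and warfarin in PO-5 and PO-6. A thrombotic emergency after a drug is stopped can appear only in the any-cause outcomes, and AO-7 and AO-9 may by then have released the patient. Admissions are part of the second trial objective, and the cost-effectiveness section also uses reductions in hospitalisation.

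**Working it through.** The plan states no figure on this point, so there is none to reproduce. The check traces each denominator through Table 4 and then counts weeks.

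**1. Who can leave on stopping a drug**

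| Outcomes | Risk factors that persist | Risk factors that lapse after 12 weeks |
|---|---|---|
| AO-1, AO-4, AO-7 (GI) | ulcer code; age 75 or over | aspirin at age 65 or over; warfarin |
| AO-2, AO-5, AO-8 (heart failure) | heart failure code | none |
| AO-3, AO-6, AO-9 (renal) | CKD stage 3 to 5 | diuretic plus ACE inhibitor/ARB |

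Exit is therefore possible only for:
- GI: a patient aged 65 to 74 on aspirin, or under 75 on warfarin, with no ulcer code and no other qualifying drug.
- Renal: a patient on a diuretic plus ACE inhibitor/ARB without CKD 3 to 5.

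Example: a patient aged 68 takes aspirin and clopidogrel without gastroprotection (PO-4), with no ulcer code and no warfarin. If aspirin is the drug stopped, the patient leaves the GI denominator 12 weeks after the last aspirin prescription. A later stroke is missing from AO-7. It is counted elsewhere only if the patient is also in the heart failure or renal group.

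AO-1 and AO-3 share these denominators. They count only admissions preceded by a high-risk prescription as defined in Table 4, so after exit no event could qualify by the lapsed route. The outcomes that lose countable events are AO-4, AO-6, AO-7 and AO-9.

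**2. Weeks lost for such a patient**

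Inputs: look-back of 12 weeks (Table 4); follow-up F = 48 weeks (Figure 1 legend), or 52 if the year in the footnote is a calendar year; t = week of the last qualifying prescription.

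Uncounted weeks = max(0, F − t − 12), out of F − t remaining.

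| t | F = 48 | F = 52 |
|---|---|---|
| 4 | 32 of 44 (73%) | 36 of 48 (75%) |
| 12 | 24 of 36 (67%) | 28 of 40 (70%) |
| 24 | 12 of 24 (50%) | 16 of 28 (57%) |
| 36 | 0 of 12 | 4 of 16 (25%) |

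If t is uniform over follow-up (an assumption), the mean number of uncounted weeks is (F − 12)² / (2F):
- F = 48: 36² / 96 = 13.5 of a mean 24 remaining (56%).
- F = 52: 40² / 104 = 15.4 of a mean 26 remaining (59%).

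**3. From one patient to the trial**

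The overall loss needs two quantities that the protocol does not give: the share of denominator patients who qualify only by prescription, and how far the intervention changes the stopping of those drugs. It cannot be computed.

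**The case against.** A reader might infer that all nine admission outcomes drop patients once treatment is stopped, that post-stopping events are never counted, and that the patient-outcome results are therefore biased in favour of the intervention. The protocol does not support this, for five reasons.

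- **Scope.** AO-2, AO-5 and AO-8 rest on a heart failure code ever recorded. Age 75 or over, an ulcer code, CKD or another qualifying drug also keeps a patient in. A patient aged 68 on warfarin and aspirin must lose both drugs to leave the GI group.
- **Timing.** Admissions within 12 weeks of the last qualifying prescription still count.
- **Route.** The numerator drug is the NSAID in PO-3, PO-5 and PO-8, clopidogrel in PO-4, and aspirin or clopidogrel in PO-6. Stopping it does not itself remove the patient through that measure. PO-1 to PO-6 can also be cleared by a gastro-protective prescription with nothing stopped. No passage says that the intervention will increase stopping of denominator drugs.
- **Symmetry and direction.** The same rule applies before and after the start, so bias needs a change in stopping. Exit also removes person-time. If time off aspirin, warfarin or the diuretic combination carries lower GI or renal risk, removing it raises the remaining AO-4 or AO-6 rate, which works against the intervention.
- **Status.** The outcomes are secondary. The section on design of outcome measures already doubts that interventions confined to medication use will move overall admission rates.

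All of this stands, and it narrows the point. It does not remove it. The denominator rule is fixed in the outcome table, nothing else in the protocol offsets it, and using the same rule in both years does not protect the comparison if stopping changes. The absence of a thrombotic outcome is a matter of choice rather than an error.

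**Conclusion.** The point holds for a defined subgroup. In the GI and renal groups, patients who qualify solely by a current prescription are lost 12 weeks after it ends, and a prompted review can bring that about. AO-4, AO-6, AO-7 and AO-9 can be affected. The losses of 73% (last prescription at week 4) and 56% (uniform stopping) over 48 weeks apply only to patients in that subgroup whose qualifying drug is stopped; they are not trial-wide figures.

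The size of any bias is unknown and could be negligible. Its direction may be favourable for AO-7 and AO-9, if admissions caused by stopping outnumber those avoided, and unfavourable for AO-4 and AO-6. On the current definition alone, a favourable AO-7 or AO-9 result should not be read as absence of harm from stopping treatment. Severity is minor to moderate; the primary prescribing outcome is not in question here.

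**What to change.** For AO-4, AO-6, AO-7 and AO-9, pre-specify before data lock an additional analysis in which patient time starts when a risk factor is first met in the period and runs to the end of the period, death or deregistration, whatever happens to the qualifying drug. Apply it identically to the year before and the year of follow-up, and report it beside the current-risk-time version.

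Optionally, add one outcome from the same SMR01 linkage: emergency admission for myocardial infarction, ischaemic stroke or TIA, or venous thromboembolism. Events would be few and intervals wide.

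The cost is a second definition of patient time, slightly diluted rates and a little extra analysis, plus one code list if the optional outcome is added. No new data collection is needed, and no clinical rule changes.

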### Primary outcome measure

Table 3: Primary outcome measure (CPO = Composite of prescribing outcomes)

### Secondary outcome measures

#### Prescribing outcome measures-individual measures

Table 4: Secondary outcome measures (PO = Prescribing outcomes)

##### 'Repeated' versus 'New' prescribing

Table 5: Secondary outcome measures (repeated versus new prescribing)

### Admission outcome measures

Table 6: Secondary outcome measures (AO = admissions outcomes)

### Measures of wider impact on NSAID prescribing

Table 7: Measures of wider impact on NSAID prescribing (VO = volume outcomes)

### Cost-effectiveness

The cost-effectiveness of the intervention will be measured as the cost per reduction in high-risk prescribing and cost per reductions in hospitalisations from an NHS perspective.

### Data collection

#### Prescribing outcomes (PO - 1 to 9)

The primary outcome and prescribing secondary outcomes will be measured in each practice at eight weekly intervals (reflecting that the measure numerators are all for high-risk prescriptions in the last eight weeks). At the time of initial data extraction, eight weekly measures will be constructed for the 48 weeks before the intervention start date.

All outcomes will be measured in the informatics tool using identifiable patient data, but only practices will be able to view identifiable data which will remain in an NHS Tayside controlled database. Access to identifiable data will require explicit practice consent for each individual using the tool, and will be controlled by the NHS Tayside LDAP system used for all clinical systems.

During the study, the core research team will be able to view aggregate practice data (run charts of change over time for each measure) and a summary of practice activity (log-ins, reviews, actions taken). At the end of the trial, fully anonymised data will be extracted from the informatics tool database held by NHS Tayside, and transmitted to the research team using established University of Dundee Health Informatics Centre (HIC) Standard Operating Procedures (SOPs) that require robust anonymisation, transmission using appropriate secure encryption, storage of data on securely encrypted computers, and compliance with Data Protection Act regulations.

### Admission outcomes (AO - 1 to 9)

Scottish Morbidity Recording (SMR01) data on admissions will be linked by HIC to the prescribing data supplied by Aridhia, and provided to the research team under the conditions required by the HIC SOPs described above.

### Statistical methods

The analyses will be implemented under the principle of intention-to-treat and the guiding principles of the ICH E9 for the analysis of randomised controlled trials. All analyses will be carried out under the guidance of the Tayside Clinical Trials Unit, which has UK registration.

The stepped wedge design is essentially a matched design with before and after comparisons for each unit of randomisation. In this case, the unit will be a group of practices where each group is randomised to a particular starting time. In addition to practice level, patient level data will also be collected, and so the analysis is divided into practice level and patient level with the patient level analysis as the primary outcome.

### Practice level analysis

Practices will be characterised by health board, size, age range, proportion of men and women, number of GPs, and training status. The primary outcome of the composite high-risk prescribing measure (Table 3) will be summarised as the mean and standard deviation across practices for before and after the intervention started. Analysis of before compared to after intervention will be carried out using mixed models or multi-level models that account for the correlation of repeated measures (eight-week periods) and stratification by health board in two levels (Tayside and Fife; larger and smaller list sizes). The primary null hypothesis is no difference in the composite before compared to after intervention. A test of the intervention (before versus after) by health board interaction in the model will test whether results differ by health board. Mixed models have the advantage of allowing for missing data while maintaining the principle of intention to treat (ITT). These models can also incorporate adjustment for baseline differences. The practice level analyses will be secondary to the patient level analyses. This will be repeated for all secondary measures (Tables 4 to 7).

### Patient level analysis

The analysis above will be repeated including patient level as well as practice level data. This will be the primary analysis. At the patient level, the primary outcome is binary (yes, no), and so mixed models with binary outcomes will be utilised, i.e., non-linear mixed models. These incorporate the correlation of patients within practices and of repeated measurements over time. At the patient level, descriptive measures will be tabulated such as age, gender, deprivation decile of Scottish Index of Multiple Deprivation (SIMD), number of measures that are relevant to a patient (i.e., the patient meets the denominator definition), as well as the primary and secondary outcomes as percentages.

The mixed model will incorporate fixed terms for intervention (before versus. after), time (eight-week time periods) as well as the correlation of patients within practices and the correlation of repeated measurements over time as random effects. Hence, the analysis will have the element of time series analyses with multiple time points before and after intervention. The primary null hypothesis is no difference in the composite before compared to after intervention as a binary factor. Because patients can be in more than one time period and move in and out of numerators and denominators, the correlation of repeated measures for these individuals will be taken into account in the multilevel modelling. Patients are nested within practices but can be cross-classified with respect to time periods. Initially, this cross classification will be ignored and then the analyses will be repeated with cross-classification terms to assess any differences. These analyses will be repeated for all secondary outcomes.

A formal statistical analysis plan will be documented prior to data lock, and this will form the detailed protocol for analysis. All analyses will be carried out using SAS 9.2 and SPSS v18.

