### Trial design

The research team will deliver the DQIP intervention to general practices with the intention of changing professional behaviour, and cluster randomisation at practice level will therefore be used. The trial will use the stepped wedge design [17,18], with all participating practices receiving the DQIP intervention, but randomised to one of ten different start dates and with each practice functioning as their own control in a time series analysis. Practices will only have access to the DQIP tool over the duration of the trial (48 weeks), so that outcome measures during the DQIP intervention will be compared to care prior to it. Practices will be randomised to start the intervention at four weekly intervals with planned gaps to avoid Christmas/New Year and March (the end of the QOF reporting year). The stepped wedge design as it is used in this trial is illustrated in Figure 1.

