### Practice level analysis

The first assumes a practice level analysis, which is the most conservative. Estimated standard deviations are taken from the measured SD in the PINCER trial, and baseline was estimated from a general practice clinical dataset. The number of practices required is estimated to detect a 20% reduction from baseline with power of 80% with a two-sided alpha of 0.05 (Table 1).

**Table 1 T1:** Sample size estimation for practice level analysis

Standard Deviation	Difference 10% to 8%	Effect size	Number of practices
4.0%	2.0%	0.500	34
6.0%	2.0%	0.333	73
7.0%	2.0%	0.286	96

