### Patient level analysis

The second estimate assumes that patient level before and after data is available, and 15 practices are estimated to be needed. The third assumes a patient level analysis with time series data available, with three 'before' and three 'after' data points. Power is clearly adequate with approximately 10 practices (Table 2).

**Table 2 T2:** Sample size estimation for patient level analysis with time series data

Number of practices	Effect size	Power
10	0.25	83%
10	0.50	97%
10	0.75	99%
10	> 1.0	> 99%

From this analysis, it is clear that lack of power is not likely to be an issue. Because we know that there are significant differences between the two health boards in the primary care pharmacy resource available to practices, we expect to see differences in the effect size between Boards. Additionally, the literature indicates that interventions of the kind planned often (but not always) have varying effects in larger versus smaller practices. This therefore allows us to plan for well powered within strata analyses, and we plan to stratify randomisation into four strata (the combination of the two binary variables Tayside versus Fife and larger versus smaller) with 10 in each strata.

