### Randomisation and allocation concealment

The practice will be the unit of allocation, with practices randomised to an intervention start date using a stepped wedge design. On the assumption that forty practices are recruited, four practices will be allocated to each start date, and randomisation will be stratified in order to ensure balance across time points in terms of:

1. Health board (NHS Tayside and NHS Fife). The rationale is that the underlying organisational context differs, particularly in the way that primary care pharmacy and prescribing advice is organised, and in the focus of prescribing improvement work.

2. List size (larger versus smaller practices). The rationale is that there is evidence that complex interventions may be more difficult to implement in larger practices [19]

3. The stepped wedge randomisation will be computer-generated by the statistician on the project (PD) blinded to practice identity, subsequent to which the core research team (TD, AG, and BG) and participating practices will be informed of their start date.

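### The primary patient-level model lists no practice-specific intervention effect, leaves the level of its repeated-measures term open, and does not say which of two planned fits decides

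*Protocol article*

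**What the plan says.** Under Statistical methods, the protocol article makes the patient-level analysis primary and the practice-level analysis secondary. The primary model is a mixed model for a binary outcome with fixed terms for intervention and for eight-week period. Its random part is described as "the correlation of patients within practices and the correlation of repeated measurements over time as random effects". No level, practice or patient, is given for the repeated-measurement term. The section says it repeats the practice-level analysis, whose model allows for correlation between eight-week periods, accounts for the stratification, and tests an intervention-by-board interaction. It adds that correlation between measurements on the same individual will be allowed for.

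On the crossing of patients with periods it says: "Initially, this cross classification will be ignored and then the analyses will be repeated with cross-classification terms to assess any differences". It does not say which fit tests the primary null hypothesis, or what follows if the two disagree.

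Four other places bear on this:
- Randomisation and allocation concealment makes the practice the unit of allocation; with forty practices, "four practices will be allocated to each start date".
- Sample size (Patient level analysis) says "we expect to see differences in the effect size between Boards" and notes that effects often differ between larger and smaller practices.
- The Discussion makes effectiveness depend on how far each practice adopts the intervention and reaches its patients, and Table 8 plans extra contact with practices that hardly use the tool.
- Blinding states that the analyst cannot be blinded and relies on a pre-specified main analysis instead. A formal analysis plan is promised before data lock.

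**The concern.** Two separate matters are at stake.

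The first is the standard error. In a trial that randomises practices, a patient-level model gives honest intervals only if it carries the practice-level variation that bears on the intervention contrast. A practice intercept removes stable differences between practices. It does not cover an intervention effect that differs from practice to practice, nor whole-practice movements from one window to the next. If such variation exists and is left out, the model treats it as noise that averages away over hundreds of patients, when it averages only over practices (and, for period movements, over windows). The protocol itself gives reasons to expect the effect to vary.

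The second is pre-specification. With an unblinded analyst, the safeguard is that the deciding analysis is fixed beforehand. Two fits of the same model in a stated order, with no rank, leave that open.

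**Working it through.** **The plan's own figures.** Table 1 uses "power of 80% with a two-sided alpha of 0.05", a fall from 10% to 8%, and SDs of 4, 6 and 7 points. With d = difference/SD and n = ((1.960 + 0.842)/d)²:
- d = 0.500 gives 31.4; the paired t-test gives 34 (stated 34).
- d = 0.333 gives 70.8; the paired t-test gives 73 (stated 73).
- d = 0.286 gives 95.96, so 96 (stated 96); the paired t-test gives 98.

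So Table 1 reproduces as a one-sample or paired calculation. Its SDs are used as if they were SDs of practice-level change, but the text says only: "Estimated standard deviations are taken from the measured SD in the PINCER trial". They may describe spread between practices, so I do not use them as estimates of effect heterogeneity. Table 2 gives no patient counts or correlations. The document therefore supplies no value for either variance component.

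**Inputs from the document.** Practices are "randomised to one of ten different start dates", four per date, 40 in all, with starts four weeks apart. Each practice has six eight-week windows before and six during the intervention (48/8 = 6). Baseline p = 10%, so p(1 − p) = 0.09.

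**Assumptions.** At-risk patients per practice per window, m = 300, 800 or 1,200; the SDs in the table below; linear probability scale; planned calendar gaps ignored; no within-patient correlation unless stated.

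**Method.** Let X hold the intervention and period terms, V the covariance the model assumes (practice intercept plus patient noise), and T the covariance with the omitted component added. The model variance is A = (X'V⁻¹X)⁻¹, and the true variance is A X'V⁻¹TV⁻¹X A. With r = true SE/model SE, coverage is 2Φ(1.96/r) − 1.

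**Model SE.** 0.355 points at m = 300. It scales as 1/√m: 0.355 × √(300/800) = 0.217 (0.218 computed directly), and 0.355 × √(300/1,200) = 0.178.

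| Omitted component (assumed SD) | m = 300: r, coverage | m = 800: r, coverage | m = 1,200: r, coverage |
|---|---|---|---|
| None | 1.00, 95% | 1.00, 95% | 1.00, 95% |
| Practice-specific effect, 1 point | 1.10, 92.6% | 1.24, 88.5% | 1.35, 85.4% |
| Practice-specific effect, 2 points | 1.35, 85.3% | 1.79, 72.7% | 2.07, 65.6% |
| Practice-by-period, 0.9 points | 1.13, 91.8% | 1.31, 86.5% | 1.44, 82.6% |

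**Hand checks at m = 800.**
- Effect SD of 1 point: the true variance is close to 0.218² + 1²/40 = 0.0475 + 0.0250 = 0.0725, so SE ≈ 0.269. The full calculation gives 0.271, and 0.271/0.218 = 1.24.
- Practice-by-period SD of 0.9 points: r ≈ √(1 + 0.009² × 800/0.09) = √1.72 = 1.31.

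**Sensitivity.** A within-patient correlation of 0.3, correctly modelled, lowers coverage at m = 800 and effect SD 1 point to about 86%. Smaller practice-by-period SDs matter little: over 300 to 600 patients and within-patient correlations of 0 to 0.5, r is 1.01 to 1.04 at 0.25 points and 1.04 to 1.15 at 0.5 points.

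**Effect of ignoring within-patient correlation.** At m = 300, a model that ignores it has SE 0.355. The true SE is 0.298 if the correlation is 0.3 and 0.252 if it is 0.5. The interval is then 0.355/0.298 = 1.19 or 0.355/0.252 = 1.41 times as wide as it should be, so the error is conservative.

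**The case against.** The strongest reply is that much of this is detail for the promised analysis plan, and that the text can be read more kindly. Several stronger readings that a reader might infer do fail.

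- *That the model excludes a practice-by-period effect.* Not shown. The repeated-measurement term has no stated level, and the practice-level analysis that it repeats already allows for correlation between periods. The component is neither named nor ruled out.
- *That ignoring cross-classification makes the interval too narrow.* It does not. For persistent within-patient correlation, the calculation above goes the other way.
- *That coverage falls to about 69% at an effect SD of 1 point and 800 patients.* That follows from a raw before/after contrast: SE = √(0.09 × 2/(6 × 800)/40) = 0.097 points, against 0.185 when 1²/40 is added. The plan has fixed period terms, which raise the model SE to 0.218 and leave coverage at about 88%.
- *That effect heterogeneity inflates the type I error.* If the intervention does nothing in any practice, there is no heterogeneity and no inflation from that source. Inflation needs effects that differ between practices around a zero mean. A practice-by-period component inflates the error even under a strict null.
- *That two primary results exist.* The second fit may be meant as a sensitivity analysis. The text simply does not rank the two.

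The board interaction and the allowance for strata also absorb part of the expected variation. They do not absorb differences between practices within a board and size stratum, which is where adoption and reach would act.

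What remains is not mere silence. The article itself lists the terms of the primary model and sets the order of the fits. Its analysis plan is due only before data lock, while the core team can view aggregate practice data throughout.

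**Conclusion.** The point holds in conditional form. The primary model as listed has no practice-specific intervention effect, although the protocol expects the effect to vary, and it does not settle whether practice-by-period variation is modelled. If either component is non-zero and omitted, the primary interval is too narrow. On the documented layout, an effect SD of 1 point gives coverage of about 93%, 88% and 85% at 300, 800 and 1,200 patients per practice; 2 points gives about 85%, 73% and 66%. These figures rest on assumed patient counts and SDs and on a linear-scale approximation to a non-linear model. They show direction and plausible size, not what will happen, and the loss is nil if the components are zero.

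Independently of those assumptions, the protocol does not say which of its two fits tests the primary hypothesis, and this sits badly with its reliance on pre-specification. The matter should be corrected; it does not undermine the design.

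**What to change.** State one primary analysis: the cross-classified fit, with the fit that ignores cross-classification labelled as a sensitivity analysis. In that model include a random practice intercept, a random practice-by-period effect, a random practice-level intervention effect, and a patient effect crossed with period. Alternatively, keep a simpler model and use standard errors clustered by practice. In either case apply a small-sample correction for 40 practices, and say in advance which option is used if the full model does not converge.

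The cost is a few sentences of analysis wording and more computing time for a binary mixed model with crossed effects. Where the added components are non-zero, the intervals will be somewhat wider. No change to data collection or to the design is needed.
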